#### Secondary outcomes

##### Health-related outcomes

The probability to achieve the recommended glycaemic target (HbA1c <7.0% [53mmol/mol]) at 6 months in each group will be compared.The change in participants’ CV risk score (5-year CHD probability) will be evaluated at 3 and 6 months. Personalised CV risk scores will be calculated by the JJ risk engine based on participants’ personal characteristics and risk factors, including age, sex, body mass index, duration of T2DM, smoking status, HbA1c level (%), systolic blood pressure (mm Hg), HDL cholesterol (mg/dL), total cholesterol (mg/dL), and urine albumin creatinine ratio (mg/gCre). Systolic blood pressure will be measured at the GP practice by the standard method recommended by the Japanese Society of Hypertension [52].The change in HbA1c levels will also be evaluated at 3 months.

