#### Individual participants

Potential participants will be identified through screening of practice records by the practice staff. GPs will review the generated lists to make sure that only individuals meeting the eligibility criteria are included (see Table 1). Reasons for exclusion will be recorded. The practice staff will contact potential participants by mail and/or telephone to introduce the research and to invite them to participate in the study.

**Table 1 Tab1:** Inclusion and exclusion criteria

	**Inclusion criteria**	**Exclusion criteria**
GP practices	• At least one JPCA-Certified Family Physician willing to participate in the study	
Individual participants	• Adult aged between 20 and 69 years • Diagnosed as T2DM with HbA1c ≥ 7.0% at the last routine clinical check • Capable to fill in questionnaires in Japanese • Written informed consent	• Insulin users • Co-morbidities or disorders less compatible with behavioural management at the time of the study (e.g. cancer, substance abuse, significant mental health disorders) • Learning or communication difficulties

Patients who express an interest in participating will be invited to attend a screening appointment at the practice, where the study will be fully explained and discussed with their GP. It will be clearly stated that the study is optional and that participants are free to withdraw at their own request and at any time, without prejudice to future care. Patients will also be informed that the allocation of their practice to intervention or control group will be random. Informed consent will be secured from all eligible participants willing to participate following this face-to-face introduction to the research (see study flow in Fig. 1).

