#### Control group

Participants in the control group will receive standard diabetes care. In the absence of a concrete description in the Japanese Clinical Practice Guidelines [8], ‘standard diabetes care’ during visits will be defined as follows:Data gathering and review of the following items:◦ Symptoms
(energy levels, polydipsia/polyuria, recurrent infections, vision, sensory disturbance/
weakness, sexual functioning, chest pain, shortness of breath)◦ Monitoring
(medication adherence, immunisation uptake)◦ Social
history (smoking, alcohol, diet, exercise, depression and anxiety, driving, occupation)◦ Red
flags for diabetic ketoacidosis (vomiting, confusion, difficulty in breathing),
hyperosmotic nonketotic coma (extreme thirst, polyuria, drowsiness, nausea, high/low
blood sugars)Examination (body mass index, blood pressure, peripheral pulses, and foot care for infections, ulceration and footwear)Investigation (urine for urinalysis and microalbuminuria; blood for glucose, HbA1c, lipids, urea and creatinine)Request to make another appointment 3 months later

GPs in both groups will be asked to strictly adhere to these guidelines to make sure that ‘standard diabetes care’ is provided as consistently as possible across practices.

For comparison purposes regarding a certain number of secondary outcomes (see below), participants in the control group will also be communicated their personalised CV risks. However, this will take the form of a more conventional probabilistic risk information. They will receive a personalised CV risk score expressed as the 5-year risk probability of experiencing fatal or nonfatal coronary heart disease (CHD, i.e. angina pectoris or myocardial infarction) calculated by the JJ risk engine [51], and discuss appropriate risk reduction strategies with their GP. There will be no special criteria for discontinuing or modifying allocated interventions.

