### Outcomes

#### Primary outcome

The primary outcome will be the change in HbA1c levels at 6 months in the FEEDBACK intervention group compared with the control group. HbA1c levels will be derived from the samples collected by venepuncture at baseline, 3 months, and 6 months, obtained by the NGSP (National Glycohaemoglobin Standardisation Programme) certified method.

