### Data collection

Eligible patients who agree to participate in the study following the face-to-face screening appointment will be notified of the start of the trial by the practice staff (i.e. once recruitment of all study participants is completed and all clusters are randomly allocated to intervention or control group). They will be informed that their next routine diabetes visit will be the baseline visit of the study.

On the day of the baseline visit, before seeing the GP, demographic information (age, sex, marital status, education level, employment status), diabetes-related characteristics (duration of T2DM, history of complications, current medications) and baseline measures will be collected using standardised forms or extracted from practice records by the practice staff. Baseline measures collected before the consultation include objective numeracy level assessed using the Japanese-language version of the Lipkus scale [66, 67] and relevant outcome measures described in Table 3. Right after the consultation, additional outcome measures will be collected (see Table 3).

The same procedure will apply at follow-up visits. The member of the practice staff in charge of data collection will make sure that the questionnaires are properly filled out and that no information is missing. Questionnaires will be linked to individual participants using practice and participant ID numbers that will preserve anonymity.

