## Trial status

Protocol date: 18/01/2023. Protocol version: 1.0. Recruitment of participants started in December 2022 and is expected to be completed in April 2023. Data collection is scheduled to be completed by March 2024, after which the final data analysis will be performed and the findings presented in a separate publication.

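### The glycaemic-target outcome measures being below 7.0% at 6 months, not newly reaching it, and its model adjusts for baseline HbA1c only if a baseline significance test triggers it

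*Protocol article*

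**What the plan says.** All places are in the protocol article.

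- **Outcome** (Health-related outcomes): "The probability to achieve the recommended glycaemic target (HbA1c <7.0% [53mmol/mol]) at 6 months in each group will be compared". Table 3 marks it at the 6-month visit only.
- **Eligibility** (Table 1): "Diagnosed as T2DM with HbA1c ≥ 7.0% at the last routine clinical check".
- **Baseline sample** (Primary outcome): "HbA1c levels will be derived from the samples collected by venepuncture at baseline, 3 months, and 6 months". This is a new measurement, and no section sets a threshold for it.
- **Timing** (Data collection): the trial starts "once recruitment of all study participants is completed and all clusters are randomly allocated to intervention or control group". Participants are then told that "their next routine diabetes visit will be the baseline visit of the study". Trial status adds: "Recruitment of participants started in December 2022 and is expected to be completed in April 2023". Standard care in the Control group section includes "Request to make another appointment 3 months later".
- **Analysis** (Primary analyses): intention to treat, with a logistic mixed model for binary outcomes. Treatment group and practice size are always in the model. Baseline values enter for variables identified as potential confounders, which the Descriptive statistics section defines by a between-group difference at p≤0.10.

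**The concern.** The trial recruits people with suboptimal control, so a reader will take a rising probability of achieving the target as uncontrolled patients being brought under 7.0%. The definition does not say that. A patient at 6.8% at baseline and 6.8% at 6 months counts as a success.

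Such patients are to be expected. Selecting on a single value at or above 7.0% brings regression to the mean even if the next sample follows soon. Here routine care also continues through the wait for recruitment and allocation to finish. The length of that wait is an inference: it could be several months for a patient recruited in December and is shorter for late recruits.

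Two things are at stake. One is the meaning of the reported proportions. The other is precision and face validity: baseline HbA1c can be expected to predict this outcome strongly, yet its place in the model depends on a significance test.

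**Working it through.** **1. The plan's own figures.** No sample size or power is stated for this outcome. The primary-outcome figures reproduce:
- Per arm without clustering: 2 × (1.1 × (1.960 + 0.842) / 0.5)² ≈ 76.
- Design effect: 1 + ((0.33² + 1) × 15 − 1) × 0.035 = 1.548, stated as 1.55.

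Step 4 borrows the design effect. Applying it to a proportion is an assumption.

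**2. How many could already be at target?** The inputs below are assumptions: normal HbA1c in the source population with mean 7.0 to 7.5% and SD 0.8 to 1.1%, and a correlation ρ of 0.6 to 0.9 between successive measurements (screening to baseline, baseline to 6 months). Patients with screening HbA1c ≥7.0% are kept and controls have no trend. The last two columns apply a uniform 0.5-point benefit.

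| Mean, SD, ρ | Below 7.0% at baseline | Controls below 7.0% at 6 months | Of these, already below at baseline | Risk difference, all | Risk difference, baseline ≥7.0% |
|---|---|---|---|---|---|
| 7.0, 0.8, 0.6 | 29.5% (78 of 264) | 38.2% | 49.9% | 25.6 | 27.0 |
| 7.2, 1.1, 0.7 | 21.8% (about 57) | 29.0% | 47.7% | 18.5 | 18.3 |
| 7.5, 0.8, 0.9 | 8.0% (21) | 11.1% | 45.8% | 23.5 | 22.8 |

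Over the whole grid, 8 to 30% were below 7.0% at baseline, and about 40 to 50% of controls at target at 6 months had been there at baseline. A different model (constant true HbA1c with a skewed distribution, source mean 7.3 to 7.6%, between-patient SD 0.9, independent occasion noise of SD 0.3 to 0.6) gave 11 to 24% and 44 to 51%.

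**3. Does it distort the contrast?** Hardly. The risk difference in all participants and in those ≥7.0% at baseline differs by at most about 1.4 points (25.6 against 27.0).

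**4. How far can a chance imbalance carry over?** Take 132 per arm (264 / 2) and the middle row.
- 95% range of the imbalance in the share below 7.0% at baseline: 1.96 × √(2 × 0.218 × 0.782 × 1.55 / 132) = ±12.4 points.
- At target at 6 months if below at baseline: 0.290 × 0.477 / 0.218 = 0.635.
- At target at 6 months if not below at baseline: 0.290 × 0.523 / 0.782 = 0.194.
- Carry-over: 0.635 − 0.194 = 0.44, so 12.4 × 0.44 ≈ ±5.5 points.

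The same steps give 13.7 × 0.375 ≈ ±5.1 for the first row and 8.1 × 0.57 ≈ ±4.6 for the third.

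**5. Adjust or restrict?**
- *Restricting.* Using the second model of step 2, a 0.5-point benefit, 119 per arm and design effect 1.55, the z-statistic fell in all four scenarios: 3.71 to 3.51, 2.55 to 2.22, 3.54 to 3.37 and 2.51 to 2.23. In a separate power simulation, restriction also lost power in all four assumed scenarios (for example 0.51 to 0.38).
- *Adjusting.* In that power simulation, always adjusting for baseline HbA1c raised power in all four scenarios (for example 0.71 to 0.89). Clustering was not modelled, so this shows direction only.

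**The case against.** The strongest reply is that nothing here biases the trial. The Randomisation section places recruitment before allocation, so patients already below 7.0% are expected equally in both arms, and step 3 shows the contrast barely moving. That stands. A reader might infer that the outcome manufactures a treatment effect, or that an imbalance would read directly as one. The documents do not support either: carry-over is partial, and what remains is ordinary sampling error that the model's interval is meant to cover.

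Being at target at 6 months is also a legitimate endpoint, and holding control is a benefit. That stands too, and it argues for naming the outcome accurately, not for redefining it.

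A reader might also conclude that the main analysis should be limited to patients at or above 7.0% at baseline. That would drop randomised patients from the stated intention-to-treat analysis and lose precision. It would not remove regression to the mean either: with no true change, 6 to 16% of restricted controls would still fall below 7.0% in the second model.

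The p≤0.10 rule is said to deal with a large imbalance. It does so only in part. It is a test-driven choice, and imbalances short of the threshold are left unadjusted. As an illustration, if the rule were applied to the share below 7.0% with an unclustered test, a difference of up to 1.645 × √(2 × 0.218 × 0.782 / 132) ≈ 8.4 points would not trigger it.

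Finally, covariates for a secondary outcome are often left to an analysis plan. Here, however, the article states the covariate rule, so the point concerns what is fixed, not what is absent.

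**Conclusion.** The point holds in a limited form. As written, the outcome measures being below 7.0% at 6 months, and its model does not guarantee adjustment for baseline HbA1c. The textual part needs no assumption. The size does: 8 to 30% already below 7.0% at baseline, and a carry-over of about ±5 percentage points, rest on assumed HbA1c distributions, assumed correlations and a design effect borrowed from the primary outcome.

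There is no systematic bias between arms, and the primary analysis of HbA1c change is not touched. The consequences are a label that invites misreading and avoidable noise in one secondary comparison.

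**What to change.** - **Primary analyses section:** for this outcome, include baseline-visit HbA1c as a prespecified continuous fixed covariate in the logistic mixed model, whatever any baseline test shows. Keep all randomised participants as the main analysis.
- **Health-related outcomes section:** describe the outcome as being at target (HbA1c below 7.0%) at 6 months.
- **Reporting:** give the number and share below 7.0% at baseline by arm. Present the analysis restricted to baseline HbA1c ≥7.0% as supportive only. The baseline sample is scheduled before the first consultation, so this subgroup is not defined by a response to the intervention.

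The cost is a few lines of text. The baseline value is already collected for the primary outcome and no patient is lost from the main analysis. The odds ratio becomes conditional on baseline HbA1c, which the report should state.

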##### Behavioural outcomes

Changes in participants’ behavioural management will be measured using the Japanese-language version of the validated Summary of Diabetes Self-Care Activities Measure (SDSCA) instrument [53, 54] at each visit. The SDSCA contains 6 scales evaluating six dimensions of behavioural management: (1) dietary behaviour, (2) physical exercise, (3) SMBG, (4) medication adherence, (5) foot care, and (6) smoking. Higher scores reflect a greater number of days per week during which self-care activities are carried out (range 0–7). Only the scales numbered (1), (2), (4), and (6) will be used in this study.Changes in prescribed medications in terms of drug and/or dosage (increased, unchanged, or decreased) will also be recorded at each visit.

##### Psychosocial outcomes

Doctor-patient communication will be evaluated using the dedicated 8-item subscale of a validated Japanese-language version of the General Practice Assessment Questionnaire (GPAQ) [55, 56] and a translated version of the 4-item ‘Ask, Understand, Remember Assessment’ (AURA) instrument [57, 58], after each visit. The GPAQ items focus on GP’s interpersonal and communication skills (patients will be asked to rate them on a scale of 1 to 6), while the AURA instrument assesses patient communication self-efficacy on a 1 to 4 scale.Participatory decision-making will be measured using a 7-item subscale of the validated Japanese-language version of the Patient Assessment of Chronic Illness Care (PACIC) scale, at baseline and at 6 months [59]. Participants will be asked how often over the past 6 months their GP performed any of six behaviours associated with participatory decision-making. The five response categories range from 0 (‘almost never’) to 5 (‘almost always’).Psychosocial self-efficacy will be measured at baseline, 3 and 6 months, using a validated Japanese-language version of the Appraisal of Diabetes Scale (ADS) [60, 61], a questionnaire developed to evaluate patients’ awareness of the psychological burden of T2DM and their ability to manage this burden. The ADS uses three subscales: four questions on the subjective impact of T2DM, two questions on the sense of self-control regarding T2DM, and one question on self-efficacy in diabetic control. Each item is rated on a 5-point Likert scale, with lower scores indicating better performance.Recall of the CV risk score (effective heart age or 5-year CHD probability) will be assessed as correct or incorrect based on open numerical responses (i.e. depending on whether or not the participant gives the exact right answer) immediately after the baseline visit, and at 3 months, immediately before the 2^nd^ visit.Emotional response to the CV risk score will be assessed by a 3-item, 7-point Likert scale, ranging from ‘not afraid/anxious/worried at all about the risk score’ to ‘very afraid/anxious/worried about the risk score’, immediately after the baseline visit [62].Perceived credibility of the CV risk score will be assessed by a 4-item (‘I felt that the number received was ‘my number’; ‘I found the number to be written personally for me’; ‘I felt that the information was relevant to me’; ‘I felt that the information was designed specifically for me’), 7-point Likert scale (from ‘completely disagree’ to ‘completely agree’) adapted from previous similar research, immediately after the baseline visit [63].Intentions to change behaviour according to the Theory of Planned Behaviour [64] will be measured using a translated version of the dedicated items of the Determinants of Lifestyle Behaviour Questionnaire (DLBQ) [65], before and after the baseline visit. Each item is associated with a different self-care activity (eating healthier, increasing physical activity, and quitting smoking) and is rated on a 5-point Likert scale, ranging from ‘strongly agree’ to ‘strongly disagree’.

Table 3 provides a summary of study outcome measures and assessment time points.

**Table 3 Tab3:** Summary of outcome measures and assessment time points

**Outcome**	**Measurement method**	**Baseline visit**		**Follow-up (3 months)**		**Follow-up (6 months)**	
		Before visit	After visit	Before visit	After visit	Before visit	After visit

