### Objectives

The primary objective of this cluster randomised controlled trial (RCT) is to evaluate the effects of a personalised, multicomponent intervention (‘FEEDBACK’) aimed at engaging adults with T2DM in behavioural management more effectively. FEEDBACK is a resource-minimising intervention designed to be delivered by general practitioners/family physicians (GPs) in primary care settings. Primary endpoints of the study will be the change in HbA1c levels at 6-month follow-up.

The secondary objective is to examine whether the FEEDBACK intervention increases the quality of the doctor-patient partnership, i.e. whether it improves doctor-patient communication and participatory decision-making from a patient perspective. Finally, the tertiary objective is to investigate the effects of FEEDBACK on a range of patients’ psychological outcomes.

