##### Feedback

At the follow-up visit, participants’ effective heart age will be updated. If behaviour change does not meet expectations, participants and GPs will discuss whether the behaviour change goal is appropriate and if the action plan needs to be applied more rigorously, modified, or abandoned (in which case alternative strategies will be considered). Another cycle will then start from that point onwards and up to the next follow-up visit.

Overall, the intervention will be implemented during three routine visits including the baseline visit — i.e. over 6 months — and be delivered besides standard diabetes care (see below).

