**Psychosocial outcomes**							
Doctor-patient communication							
GP communication	GPAQ [55, 56]		X		X		X
Patient communication self-efficacy	AURA [57, 58]		X		X		X
Participatory decision-making	PACIC [59]	X					X
Psychosocial self-efficacy	ADS [60, 61]	X			X		X
Recall of CV risk score	Open-ended question		X	X			
Emotional response to CV risk score	Dedicated Likert scale [62]		X				
Perceived credibility of CV risk score	Dedicated Likert scale [63]		X				
Intentions to change behaviour	DLBQ [65]	X	X				

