#### Primary analyses for primary and secondary outcomes

The planned primary analyses will be carried out at the individual level, according to the intention-to-treat (ITT) principle. Between-group comparisons will be analysed using multilevel analysis to account for the dependency of observations. Between-group differences in the mean changes in primary and secondary outcomes will be estimated using linear mixed-effects models for continuous outcomes and logistic mixed-effects models for binary outcomes. Random effects will account for within-practice clustering and within-patient correlation. Fixed effects will be treatment group indicator (with the control group as the reference category), practice size (stratification variable) [68] and, where relevant, time indicators, their interaction effects, and baseline values of variables identified as potential confounders. In case normality assumptions are violated, outcome variables will be log-transformed and, if necessary, non-parametric tests will be used. Data analyses will be performed using Stata/MP 17 (StataCorp).

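### GPAQ and AURA are first scored after the first intervention session, so a comparison of mean changes drops whatever communication effect that session has already produced

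*Protocol article*

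**What the plan says.** All references are to the protocol article.

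- **Objective.** The secondary objective asks "whether it improves doctor-patient communication and participatory decision-making from a patient perspective" (Objectives). GPAQ and AURA are the only measures of the communication part; PACIC covers participatory decision-making.
- **Timing of the two instruments.** Psychosocial outcomes schedules them as follows: "AURA) instrument [57, 58], after each visit". In Table 3 the GP communication row (GPAQ) and the row "Patient communication self-efficacy" (AURA) are marked only in the three after-visit columns. Data collection fits this: "Right after the consultation, additional outcome measures will be collected (see Table 3".
- **What the baseline visit is.** Under Feedback, "the intervention will be implemented during three routine visits including the baseline visit". Data collection puts the start of the trial after allocation: "once recruitment of all study participants is completed and all clusters are randomly allocated to intervention or control group".
- **Planned contrast.** Primary analyses for primary and secondary outcomes states: "Between-group differences in the mean changes in primary and secondary outcomes will be estimated using linear mixed-effects models for continuous outcomes". The fixed effects are treatment group, practice size and, where relevant, time indicators, interactions and baseline values of potential confounders.
- **Comparison with other questionnaires.** PACIC, SDSCA, ADS and DLBQ each have a measurement before the baseline consultation in Table 3.

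**The concern.** A change score isolates a treatment effect when its starting value is unaffected by treatment. For GPAQ and AURA the only starting value available is the score given just after a consultation in which the intervention arm has already had risk communication, goal setting, action planning and a signed contract. GPAQ asks about the GP's interpersonal and communication skills, which is the kind of response that could plausibly move at the first such consultation.

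If the stated contrast is followed for these instruments, an early benefit is subtracted from a later one. A benefit that appears at once and is sustained would look like no difference. One that is largest at the first visit would give a negative estimate. The trial could then report a weakened, null or reversed result on communication although patients rated communication better throughout.

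**Working it through.** **1. The plan's own figures.** The protocol gives no sample size or effect size for GPAQ or AURA. Its HbA1c calculation supplies a scale for the illustration, so it is reproduced first.

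- Individual randomisation: difference 0.5, SD 1.1, two-sided α 0.05, power 80% give 76 per arm (stated: 76). The t-based value rounds up to 77.
- Design effect: 1 + ((0.333² + 1) × 15 − 1) × 0.035 = 1.548 (stated: 1.55).
- Clustered size: 77 × 1.548 = 119.2 (stated: 119).
- With 10% loss: 2 × 119 / 0.9 = 264.4 (stated: 264).

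These figures reproduce to within rounding and are not in question.

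**2. What the change contrast estimates.** Let d1, d2 and d3 be the true group differences (FEEDBACK minus control) in post-visit score at baseline, 3 and 6 months. Then

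E[Y3 − Y1 | FEEDBACK] − E[Y3 − Y1 | control] = d3 − d1.

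If a share f of the 6-month effect is present after session 1, then d1 = f × d3 and the contrast is (1 − f) × d3.

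**3. What the same mixed model can give.** With all three post-visit scores as outcomes and group, time and group-by-time terms, the group coefficient is d1 and the interactions are g2 = d2 − d1 and g3 = d3 − d1.

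- Mean-change contrast: g3 = d3 − d1.
- Level difference at 6 months: d1 + g3 = d3.
- Average over visits: d1 + (g2 + g3)/3 = (d1 + d2 + d3)/3.

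**4. Size, by illustration.** These inputs are assumptions and are not in the documents: d3 = 0.5 SD; within-patient correlation ρ from 0.3 to 0.7; effective size 119/1.55 ≈ 77 per arm, used for both contrasts. The SD of change is √(2(1 − ρ)). Power counts only rejections in favour of FEEDBACK at two-sided 0.05.

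| Share f after session 1 | Change contrast (SD) | Power, ρ = 0.3 | Power, ρ = 0.5 | Power, ρ = 0.7 |
|---|---|---|---|---|
| 0 | 0.50 | 75% | 87% | 98% |
| 25% | 0.375 | 50% | 64% | 85% |
| 50% | 0.25 | 26% | 34% | 52% |
| 75% | 0.125 | 10% | 12% | 17% |
| 100% | 0 | 2.5% | 2.5% | 2.5% |

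The level difference at 6 months stays at 0.50 SD with about 87% power in every row.

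**5. Simulation check.** In 2,000 simulated trials with 20 practices of 13 patients, ICC 0.035, ρ = 0.5 and a 0.5 SD effect fully present from the first visit, the mean change contrast was −0.003 SD and the mean 6-month level difference was 0.497 SD.

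**6. Adjusting for the first score instead of subtracting it.** On the same simple model the adjusted contrast is d3 × (1 − ρf). With f = 100% and ρ = 0.5 that is 0.5 × (1 − 0.5) = 0.25 SD, so adjustment would also remove part of the effect.

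**The case against.** The best defence is that the plan does not really fix a change-from-first-visit contrast for these two instruments. Psychosocial outcomes says that communication is evaluated after each visit, while the HbA1c, risk score and self-care outcomes are described as changes. The mean-changes sentence cannot be literal for every secondary outcome: emotional response and perceived credibility are measured once, and target attainment only at 6 months. The model already holds the terms that give level differences, so no information is lost. Post-visit scores in both randomised arms are a valid comparison without any baseline.

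Most of this stands. The wording is loose, and step 3 shows that the right contrast comes from the planned model. But the sentence covers secondary outcomes without exception, and the protocol names no other contrast for GPAQ and AURA. This is a stated target that does not fit the measurement schedule, which goes beyond detail left to an analysis plan.

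A reader might infer three stronger things that the documents do not support.

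- *That the whole effect is cancelled.* This needs an effect that is complete after session 1 and constant afterwards. The protocol does not say how the effect builds up, and goals are reviewed at later visits, so later gains are possible and would survive.
- *That the secondary objective as a whole would be reported as failed.* Participatory decision-making is measured by PACIC, which has a pre-visit score.
- *That the first post-visit score will be used as a baseline covariate.* Data collection separates baseline measures taken before the consultation from the additional outcomes taken after it, and the plan does not say that the latter are adjusted for.

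**Conclusion.** The point holds in a limited form. For GPAQ and AURA, the stated comparison of mean changes estimates d3 − d1 and so omits the part of the communication effect already present after the first session. That conclusion rests only on the schedule, the order of randomisation and baseline visit, and the stated contrast, all explicit in the protocol. How much is lost depends on the share present after session 1, which the documents do not give. The loss runs from nothing (f = 0) to everything (f = 100%), and the estimate turns negative if the first-visit effect exceeds the 6-month effect. The power figures are illustrative. Severity is moderate: two secondary questionnaires and one part of the secondary objective are affected; PACIC, the HbA1c analysis and the sample size are not.

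**What to change.** In the section on primary analyses for primary and secondary outcomes, add a sentence for GPAQ and AURA: the estimand is the between-group difference in post-visit score at 6 months, and its average over the three visits, from the planned mixed model with group, time and their interaction. State also that the first post-visit score is treated as an outcome: it is not subtracted, not used as a covariate, and the groups are not constrained to share a mean at that visit.

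This is a wording change with no new data, and it can be made after baseline visits have begun, preferably before any unblinded look at the data.

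Optionally, where still feasible, the 8 GPAQ and 4 AURA items could also be given before the baseline consultation, ideally before allocation, and that score used for adjustment. The cost is 12 short items alongside questionnaires already completed before that visit. A pre-consultation GPAQ rating would refer to earlier consultations, so it would serve as a covariate and would not replace the level comparison.
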